## Abstract

**Background:**

Among clinical trials of interventions that aim to modify time spent on mechanical ventilation for critically ill patients there is considerable inconsistency in chosen outcomes and how they are measured. The Core Outcomes in Ventilation Trials (COVenT) study aims to develop a set of core outcomes for use in future ventilation trials in mechanically ventilated adults and children.

**Methods/design:**

We will use a mixed methods approach that incorporates a randomised trial nested within a Delphi study and a consensus meeting. Additionally, we will conduct an observational cohort study to evaluate uptake of the core outcome set in published studies at 5 and 10 years following core outcome set publication. The three-round online Delphi study will use a list of outcomes that have been reported previously in a review of ventilation trials. The Delphi panel will include a range of stakeholder groups including patient support groups. The panel will be randomised to one of three feedback methods to assess the impact of the feedback mechanism on subsequent ranking of outcomes. A final consensus meeting will be held with stakeholder representatives to review outcomes.

**Discussion:**

The COVenT study aims to develop a core outcome set for ventilation trials in critical care, explore the best Delphi feedback mechanism for achieving consensus and determine if participation increases use of the core outcome set in the long term.

## Background

The provision of mechanical ventilatory support with accompanying sedation is a major supportive therapy in intensive care units (ICUs), but is not without potential harms. In an attempt to minimise these, research has examined the effect of various interventions to reduce unnecessary time receiving mechanical ventilation. These interventions include sedation and ventilator weaning protocols, and alternative ventilation modes. Systematic reviews of trials spanning 20 years that evaluated protocolised and automated weaning in adults and children highlight variation in how outcomes were defined, measured and reported [1–3]. Outcome variability is not limited to trials of protocolised weaning. A systematic review of 66 critical care trials that measured ventilation as a primary or secondary outcome found outcome reporting was not standardised [4]. Of 48 trials reporting duration of mechanical ventilation, 75 % did not define start and end points, and the remaining 25 % used variable definitions. Furthermore, of 25 trials measuring ventilator-free days, 36 % did not provide a definition, that is, when counting of ventilator-free days commenced and ended; of those that did, again variability was noted. Notably, although all 66 trials measured ventilation outcomes, no two trials used the same ‘set’ of outcomes to do this.

It is evident there is a need for standardisation of outcome selection and definitions, and difficulties raised by inconsistent outcome reporting are increasingly recognised. The Consolidated Standards of Reporting Trials (CONSORT) statement 2010 [5] and the Standard Protocol Items: Recommendations for Interventional Trials (SPIRIT) statement 2013 [6] both explicitly advocate the use of ‘core outcome sets’ to achieve consistency in outcome reporting. These statements refer researchers to the Core Outcome Measures in Effectiveness Trials (COMET) database for guidance [7]. A core outcome set (COS) is defined as ‘the minimum [number of outcomes] that should be measured and reported in all clinical trials of a specific condition’ [8]. The COMET Initiative was commissioned to encourage the development and application of COS across health and social care, create accessible information about guidelines on outcome selection, and facilitate collaboration among researchers developing COS. The initiative has received widespread international support from organisations, including Outcome Measures in Rheumatology (OMERACT) [9] and the International Forum for Acute Care Trialists (InFACT) [10]. InFACT aims to promote international collaboration in critical care research and address barriers in undertaking trials, and is a major driving force behind the advancement of creating COS for critical care trials [10].

Using a Delphi study followed by a consensus meeting is a widely accepted method of achieving consensus for developing COS [8], but there are variations in how feedback to the panel is provided during Delphi rounds. Currently, there is no evidence as to which feedback method will best achieve consensus that is representative of all stakeholder groups. A systematic review of studies using the Delphi technique to develop COS found no evidence to identify which methods will yield consensus that is genuinely representative of all stakeholder groups [11]. When developing a COS important factors to take into consideration are the inclusiveness of stakeholders in the Delphi panel and the mechanism used to provide feedback to the panel. Furthermore, once developed, it is important to evaluate subsequent COS uptake in clinical trials. Our Delphi study to develop a COS will address both variation in selecting and defining outcome measures for ventilation trials, and will lay the foundation for follow-up to examine uptake.

### Aims and research questions

The primary aim is to develop a COS for trials involving patients undergoing mechanical ventilation where an aim of the intervention is to modify time spent on mechanical ventilation. The secondary aims are to determine the most valid method of gaining consensus for a COS, and to evaluate the COS uptake 5 and 10 years after its publication.

Our research questions are:Which outcomes are ranked by stakeholders as critical for inclusion in the COS?How is the ranking process influenced by the method of stakeholder group feedback during Delphi rounds?Do Delphi panel participants rank the importance of outcomes differently depending on their knowledge of the other groups’ ranking?Does participation by investigators in the Delphi panel affect their subsequent use of the COS, compared with investigators who do not participate?

## Methods

We will use a mixed methods approach that incorporates a randomised trial nested within a Delphi study and a consensus meeting. Subsequently, we will conduct an observational cohort study to evaluate COS uptake in published studies at 5 and 10 years following COS publication.

### Delphi study

We will use the Delphi technique to achieve input from a broadly representative international and diverse stakeholder panel. Our Delphi study consists of a series of sequential questionnaires or ‘rounds’ aiming to obtain a consensus of opinion from a group of expert stakeholders [12]. The Delphi technique can also minimise response bias as individual feedback is anonymised and not influenced by views of influential individuals.

### The Delphi panel

A range of expertise within the panel is considered to be an important quality criterion for development of COS [11]. We will therefore seek to include representatives from seven key stakeholder groups that may be particularly interested in this COS. The groups and inclusion criteria are as follows:Industry and pharmaceutical representatives – from companies producing technology and products used in mechanical ventilation.Nurses and allied health professionals (NAHP) – members of professional societies or associations who have a primary role in clinical critical care practice with a minimum of 5 years’ experience.Physicians – members of professional societies or associations who are consultant grade (or equivalent) in intensive care, pulmonology or anaesthetics, and have a primary role in clinical practice.Research funding organisations – representatives from funding bodies that have funded or commissioned critical care research projects in the last 5 years.Patient support groups or charities – representatives from respiratory or critical care charities; patient or relatives user groups, forums or support groups, preferably with personal experience of critical care.Clinical trial groups (CTGs) – members of CTGs that may include the Chair and other appropriate members, preferably representing diverse professions.Trial investigators – primary and senior authors of reports of clinical trials evaluating interventions aiming to reduce duration of mechanical ventilation. These will be identified from a systematic search of publications in PubMed over the last 10 years.

### Panel size and recruitment

There are no generally accepted guidelines for optimal panel size to achieve stable consensus in Delphi studies [13]. Panel size in other projects has usually been guided by practicality, question scope and time available for analysis [11]. We will attempt to recruit as large a panel as possible, and will encourage all organisations within each stakeholder group to nominate between five and ten representatives who meet the inclusion criteria.

Organisations within each stakeholder group will be identified through our wide network of critical care contacts and through a methodological web-based search. We will email study information to key contacts (for example, Chair, President, Director) within organisations, inviting them to nominate expert participants or to forward a recruitment letter.

The French Cochrane Centre will undertake a systematic search of PubMed to identify trial investigators. This search will include appropriate terms for: population (adult and child); interventions (aimed at reducing duration of mechanical ventilation); year of publication (2004–2014); and study type (randomised trials, observational studies). We anticipate an overlap between eligible participants identified through the PubMed search and those identified by CTGs; therefore, we will only recruit those participants not identified by the CTGs into the trial investigator arm.

Previous studies of the Delphi technique demonstrate high attrition after four rounds [10]. Therefore, we will use three rounds and provide two-weekly reminders to participants. Other techniques to minimise attrition include: provision of a personalised invitation and reminders; an outline of timelines; and ensuring that each round is concise and easy to complete with minimal time commitment. Participants will receive an email comprising a clear study explanation emphasising the importance of completing all rounds, an estimate of the amount of time to complete the questionnaires and requesting consent for participation.

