### Consensus meeting

Following completion of the Delphi, we will invite representatives of stakeholder groups from the Delphi panel, COMET Initiative and the InFACT Outcomes Working Group to the consensus meeting. To promote wide dissemination, we also will invite editors from key journals (for example, *American Journal of Respiratory and Critical Care Medicine*, *Critical Care Medicine*, *British Medical Journal*, *The Lancet*, *Intensive Care Medicine*, *Critical Care*) and funders of critical care trials. The purpose of the consensus meeting is threefold, with the common aim of reaching a consensus among those present on the content of a core outcome set for mechanical ventilation. A report from this meeting will be written up and published.

As described in the paper, participants with differing professional backgrounds in the Delphi study will be randomised into one of three groups, each using a different feedback mechanism between rounds. Therefore, the Delphi will produce three separate proposals for the variables to include in the COS. It is likely that there will be overlap between these three sets but they may also differ in regard to the outcome variable types that they contain. However, given that there is no gold standard in Delphi studies for the best feedback mechanism to attain consensus, we cannot be sure that the consensus on a COS reached by any particular group is superior to that reached by another of the groups, using a different feedback mechanism. The research team will review the consistency or variance between the three COS. If there is consistency, then one COS will be brought to the meeting, but if there is variance we will bring this to the attention of the meeting for discussion and agreement on choosing one particular COS. This is the first purpose of the meeting.

The aim of the Delphi study is only to determine ‘what’ outcomes should be measured in mechanical ventilation trials – it is not designed to determine ‘how’ the outcomes should be measured or, specifically, the time point at which the outcome should be determined. So, the second purpose of the consensus meeting is to bring together experts in mechanical ventilation trials alongside representatives of other organisations contributing to the development and/or dissemination of core outcome measure sets, including OMERACT, InFACT and COMET, to discuss ‘how’ the outcome variables in the COS should be measured.

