### Sample identification

We will conduct a PubMed search using terms relating to mechanical ventilation, synonyms for ‘duration of mechanical ventilation’ and study design, to identify a cohort of primary and senior authors that have published a trial in this area in the past 10 years.

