## Methods

Study authors will be randomised to either participate in the Delphi panel as a ‘trial investigator’ stakeholder representative or not to participate (see Fig. 2). As we are using data available in the public domain, informed consent will not be sought from those not involved in the Delphi. Participants involved in the Delphi will be asked for informed consent in accordance with other participating stakeholder groups.

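### The clinical trial group exclusion is written for the participation arm only, and nothing keeps authors allocated not to participate off the Delphi panel, so the uptake comparison is unprotected

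*Protocol article*

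**What the plan says.** All references are to the Protocol article.

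- **Overlap.** Panel size and recruitment foresees the problem: "We anticipate an overlap between eligible participants identified through the PubMed search and those identified by CTGs". The remedy follows in the same sentence: "therefore, we will only recruit those participants not identified by the CTGs into the trial investigator arm".
- **Author cohort.** Sample identification describes a PubMed search "to identify a cohort of primary and senior authors that have published a trial in this area in the past 10 years". It mentions no removal of authors named by CTGs.
- **Allocation.** The Methods section of the observational cohort study states: "Study authors will be randomised to either participate in the Delphi panel as a ‘trial investigator’ stakeholder representative or not to participate". It sets no exclusion either, and refers to Fig. 2, which is not available in the text reviewed.
- **Other ways onto the panel.** The Delphi panel lists seven stakeholder groups. They include physicians, nurses and allied health professionals (NAHP), and CTG members, and no criterion bars a trial author from these. Under Panel size and recruitment, key contacts in organisations receive an email "inviting them to nominate expert participants or to forward a recruitment letter". Ethical requirements also allows people to volunteer themselves once nominated.
- **Comparison.** Observational cohort study asks whether investigators on the Delphi panel take up the core outcome set (COS) more than investigators who stayed off it. The Analysis section that follows compares the proportion of authors using the COS at 5 and 10 years by a chi-square test at the 0.05 level.

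**The concern.** A randomised comparison of uptake needs two things: arms drawn from the same people, and a real difference between them in panel membership. The text secures neither.

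The overlap rule speaks only of recruitment to the trial investigator side, while the cohort and allocation text has no counterpart. Followed to the letter, an author allocated to participate is dropped if a CTG has named them. An author allocated not to participate is kept, and may be sitting on the panel in the CTG group. The arms would then differ in make-up, and part of the control arm would have had the exposure.

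Separately, the physician, NAHP and forwarded-letter routes stay open to every author allocated not to participate. The cohort Methods section does not seek consent from authors outside the Delphi, so such an author may not know of the allocation and would have no reason to decline.

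At stake is the only comparison that answers the fourth research question, on whether taking part changes later use of the COS. The COS itself and the nested trial of feedback methods are not affected.

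**Working it through.** The plan states no overlap, uptake rate, sample size or power for this comparison, so there is no figure to reproduce. The check is a reading of the text, followed by arithmetic on assumed values.

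**Step 1: the two readings of the overlap rule**

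| | Removal one-sided, after allocation | Removal from the whole list, before allocation |
|---|---|---|
| Fits the sentence in Panel size and recruitment? | Yes, literally | Yes |
| Stated in Sample identification or the cohort Methods? | No | No |
| Arms comparable? | No | Yes |
| CTG-named controls on the panel? | Possible, and the overlap is expected | No, if the CTG lists are complete by then |
| Entry by physician, NAHP or forwarded letter blocked? | No | No |

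The last row is the same under both readings.

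**Step 2: one-sided removal with no true effect of participation**

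Let s be the share of CTG-identified authors in the list, u_C their uptake and u_0 the uptake of the others.

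- Participation arm: u_0
- Non-participation arm: s·u_C + (1 - s)·u_0
- Spurious difference: -s·(u_C - u_0)

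Assume u_0 = 10%:

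| s | Control uptake, u_C = 20% | Difference | Control uptake, u_C = 30% | Difference |
|---|---|---|---|---|
| 10% | 11% | -1 point | 12% | -2 points |
| 20% | 12% | -2 points | 14% | -4 points |
| 30% | 13% | -3 points | 16% | -6 points |

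A second set of assumptions uses higher uptake: u_0 = 20%, u_C = 40% or 50%, s = 10% to 40%, and 100 authors per arm before removal. The spurious difference then runs from -0.1 × 20 = -2 points to -0.4 × 30 = -12 points. The chance of a significant result against participation runs from about 5% to 37%, where 2.5% is nominal in that direction.

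The sign depends on u_C exceeding u_0. If the two are equal the difference is zero; if u_C is lower, the sign reverses.

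**Step 3: dilution by crossover**

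Let c be the share of the non-participation arm that enters the panel by another route. Assume entry by that route has the same effect as entry as a trial investigator. Control uptake is then p_0 + c·(p_1 - p_0), and the difference is (1 - c)·(p_1 - p_0).

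Assume p_1 = 40%, p_0 = 20%, 100 authors per arm and two-sided alpha 0.05:

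| c | Control uptake | Difference | Power | Authors per arm for 80% power |
|---|---|---|---|---|
| 0% | 20% | 20 points | 88% | 82 |
| 10% | 22% | 18 points | 79% | 103 |
| 20% | 24% | 16 points | 68% | 133 |
| 30% | 26% | 14 points | 56% | 176 |
| 50% | 30% | 10 points | 32% | 356 |

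**The case against.** The strongest reply is that one-sided removal is an inference. The rule sits in a section on Delphi recruitment, and the arm it names may simply be the trial investigator stakeholder group. Its purpose would then be to stop one person being counted in two stakeholder groups. It also acts on people found by the search, which fits removal before allocation. Fig. 2, which would show the order, is not available, and an article condenses a fuller protocol. This stands: a reader might infer that the randomised arms are certainly not comparable, and the document does not establish that. It does not answer the second limb, because the rule covers CTGs alone and the other nomination routes stay open in either case.

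Two further inferences should be resisted.

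- **Search frames.** The recruitment search covers observational studies as well as randomised trials, while the cohort is of trial authors. This does not make the arms differ. The Delphi panel section limits eligibility to authors of clinical trial reports, and a single pool of authors is randomised.
- **Consensus meeting.** The aim to "bring together experts in mechanical ventilation trials" might look like another way in for controls. But the sentence describes the meeting's purpose, the stated invitation list contains no general call to outside trial authors, and the exposure under study is Delphi panel membership.

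It is also fair to say that nothing in the document shows CTG-linked authors to be likelier users of the COS, and that crossover weakens the contrast without undoing the randomisation if authors are compared as allocated. Both points stand.

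**Conclusion.** The point holds in a limited form. The overlap rule is written for the participation arm alone, the author cohort is randomised with no matching rule, and the literal result is a filtered arm set against an unfiltered one. If the overlap is in fact removed before allocation, comparability is preserved, but authors allocated not to participate can still join the panel by nomination or forwarded letter.

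The sizes are illustrations. One-sided removal gives -1 to -6 points under the first set of assumptions and -2 to -12 under the second, with the direction itself assumed. Crossover of 10% to 30% cuts an assumed 20-point difference to 18 to 14 points, and power from 88% to between 79% and 56% at 100 per arm.

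Uptake is a secondary aim and the COS does not depend on it, so this is a correction worth making now and not a defect that should hold up the study.

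**What to change.** 1. State in Sample identification and in the cohort Methods that authors identified by CTGs, or already nominated through any other stakeholder group, are removed from the author list before randomisation and for both arms. Reword the sentence in Panel size and recruitment to agree.
2. Check every later nominee, volunteer and respondent to a forwarded letter against the list of authors allocated not to participate.
3. State in the uptake Analysis that authors are compared as allocated, and report the number who crossed over and by which route.

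The cost is one de-duplication, which requires the nominee lists to be in hand before authors are randomised, and a running name check afterwards. Study status says that the panel is still being recruited and the Delphi has not begun, so this remains feasible. Once controls have sat on the panel, no analysis at 5 or 10 years can restore the intended contrast. The downside is a somewhat smaller author list and a result that does not cover CTG-linked authors.

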### The Delphi questionnaire and rounds

The Delphi will be managed using a bespoke online e-management system maintained by the COMET Initiative. This system has previously been used in the Management of Otitis Media with Effusion in Cleft Palate (MOMENT) study developing a COS for trials investigating otitis media with effusion in children [14]. It has been modified for this project to accommodate data collection, randomisation process, web link to the relevant questionnaire and presentation of scoring within each round.

### Round 1

We will use the most frequently reported outcomes identified from our systematic review for the first Delphi round. Participants will be asked to score each outcome using the Grading of Recommendations Assessment, Development and Evaluations (GRADE) scale of 1–9, where 1 represents least important and 9 represents most important [15]. Participants will have the option to suggest additional outcomes for inclusion in the second round. We will list outcomes in alphabetical order to avoid potential weighting. Outcomes suggested during round 1 will be reviewed and coded by two research team members to ensure they represent new outcomes; where uncertainty exists, the advisory group will be consulted. Scores attributed to each outcome will be calculated as a percentage of the total responses for all scores. This will be summarised by stakeholder groups and all outcomes will be carried forward to round 2. A flowchart of the study is shown in Fig. 1.

